##### Autonomous motivation

To assess students’ perceptions of autonomous motivation in PE lessons, the Motivation Questionnaire for Physical Education Classes (CMEF; Sánchez-Oliva et al., 2012) will be used. This questionnaire begins with the phrase “I participate in PE classes…,” followed by eight items evaluating autonomous motivation (e.g., “…because I find it enjoyable and interesting”). Students will respond on a 5-point Likert scale, ranging from 1 (*strongly disagree*) to 5 (*strongly agree*).

##### Group processing

To assess students’ perceptions of group processing, the Cooperative Learning Measurement Questionnaire in Educational Contexts (Fernandez-Rio et al., 2017) will be used. This factor is headed by the stem “In PE classes.,” followed by four items (e.g., “…We engage in group discussions to ensure that everyone understands what is being done”). Responses will be rated on a 5-point Likert scale, from 1 (*strongly disagree*) to 5 (*strongly agree*).

##### Problematic relationships

To assess students’ perceptions of problematic relationships in the classroom, the Problematic Relationships Scale (PRS; Cheon and Jang, 2012) will be used. This one-factor scale consists of four items (e.g., “I feel uncomfortable when interacting with my classmates”). Responses will be recorded using a 5-point Likert scale, ranging from 1 (*strongly disagree*) to 5 (*strongly agree*).

##### Learning in PE

To examine students’ perceived learning, the Perceived Learning Questionnaire (PLQ, Llanos-Muñoz et al., 2025) will be used. The questionnaire begins with the phrase “In PE classes.,” followed by eight items distributed into two factors (four items per factor): acquired learning (e.g., “…I learn things I did not know before”) and functional learning (e.g., “…I learn important things that I can apply in my daily life or the future”). Responses will be measured using a 5-point Likert scale, ranging from 1 (*strongly disagree*) to 5 (*strongly agree*).

##### Academic performance in PE

To measure academic performance in PE lessons, two questions will be used: “What grade did you receive in PE last year/trimester?” and “What grade will you receive in PE this term?.” Following Spanish educational assessment policy guidelines (Spanish Government, 2020), response options will be structured on a five-level scale: 1. Fail, 2. Pass, 3. Good, 4. Very Good, 5. Excellent. These questions have been previously used in educational research (see Guntern et al., 2017; Luo et al., 2023).

### Plan of analysis

A mixed-method analysis will be conducted to evaluate the training program, as well as to assess the impact of its implementation in PE lessons on the study variables for both teachers and students. Regarding the quantitative analysis, first, a descriptive analysis will be conducted to evaluate both teachers’ and the external researcher’s perceptions of the training program, assessing aspects such as its innovation, practical relevance, and the feasibility of the strategies implemented. Second, to assess the impact of the intervention program on the study variables for both teachers and students, the nature of the variables will first be examined through tests of normality, validity, and reliability across the three measurements. Third, the assumptions of independence, linearity, and homogeneity of variance will be verified to ensure the appropriateness of analyses based on the general linear model. Fourth, between-group and within-group differences will be analyzed using repeated-measures multivariate analysis of covariance (MANCOVA). A 3 × 2 (Time × Condition) repeated measures MANCOVA will be performed for both teachers and students, with covariates such as age, sex, teaching experience, type of school, and school location for teachers, and age, sex, sociocultural background, and school grade for students. If parametric assumptions are not met, appropriate non-parametric alternatives such as the Wilcoxon signed-rank test (for within-group comparisons) and the Mann–Whitney U test (for between-group comparisons) will be used. Subsequently, to examine intragender differences of the intervention on study variables, a 3 × 2 × 2 (Time x Condition x Sex) repeated measures MANCOVA will be performed for both teachers and students. To further examine changes in each outcome variable over time (T1, T2, and T3) within each group (experimental vs. control), multiple paired t-tests with Bonferroni correction will be conducted. Effect sizes will be calculated using partial eta squared (*η^2^ₚ*). Effect size thresholds will be interpreted as small (*η^2^ₚ* > 0.01), moderate (*η^2^ₚ* > 0.06), or large (*η^2^ₚ* > 0.14) following Cohen’s criteria. For all analyses, the significance threshold will be set at *p* < 0.05. All statistical analyses will be conducted using IBM SPSS Statistics v.25.0. Finally, a longitudinal structural equation model will be employed through the statistical software Mplus (Muthén and Muthén, 1998-2019) to analyze the predictive relationships between the study variables, allowing for the observation of potential differences at the three specific times (T1, T2, and T3) when data are collected.

Regarding the qualitative analysis, the qualitative data from the focus group will be transcribed and managed using NVivo Version 11.0 to ensure systematic organization. A thematic analysis following the procedures outlined by Braun and Clarke (2019) will be employed. Initially, three researchers will independently examine the transcripts to familiarize themselves with the content. Relevant excerpts reflecting teachers’ views on the training program’s outcomes and its application with students will then be identified. After coding, final themes and subthemes will be refined to accurately capture the core meanings. The analysis will adopt a deductive approach, grounded in SDT and the CMC, given most of the questions align with these theoretical frameworks. Additionally, two researchers will oversee the process, contributing their insights to support consensus in the interpretation of results.

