**Figure 2 fig2:**
[figure not shown]
Hypothetical multilevel model of the predictive relationship between the study variables.

Previous correlational studies examining the relationship between students’ perceptions of relatedness support and various outcomes, while accounting for sex differences, have yielded mixed results (Leo et al., 2023b; Leo et al., 2022; Vasconcellos et al., 2020; White et al., 2021). In this regard, although previous studies have included sex as a covariate when analyzing the effects of SDT-based interventions, sex differences are rarely reported for either teachers or students (Vasconcellos et al., 2020). However, systematic reviews and meta-analyses have emphasized the importance of examining school-based motivational intervention effects separately for boys and girls (Vasconcellos et al., 2020). Therefore, it is crucial to account for sex differences when evaluating intervention effects to determine whether they are equally effective for both sexes. Given the inconsistent findings in previous research regarding the study variables, no specific hypotheses will be formulated regarding potential sex differences among students.

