#### Sample recruitment with inclusion criteria

Between 8–10 secondary PE teachers, assigned to the experimental group and to the control group equally, along a subset of their students, will be anticipated to take part in this study. Given the research team’s limited resources, the maximum number of participating teachers will be set at ten. Randomization will be performed using a digital tool. To minimize the risk of cross-contamination between conditions, teachers from the same high school will not participate. Teachers will be recruited through multiple channels, including social media platforms, telephone calls, and emails. Specifically, information (e.g., flyers and recruitment letters) will be shared via professional networks, PE-related social media groups, and the regional government’s official teacher registry. School principals will also be contacted directly to help disseminate the invitation within their schools.

The registration period will last approximately 2 weeks. Teachers whose participation is not approved by their school leadership will not be included. If more than 10 teachers, or multiple PE teachers from the same school, express interest, a waiting list will be created. Final selection will be based on predefined inclusion criteria and logistical feasibility, including school location, number of participants per school, schedule compatibility, and the research team’s capacity to monitor and support the intervention.

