Teachers must meet the following inclusion criteria to participate in this study: (1) be an in-service PE teacher at the same school for the entire academic year; (2) complete the study questionnaires at three different time points; (3) not participate during the entire academic year in other intervention or training programs similar to this study; (4) attend all the training program sessions; (5) allow research team visits for classroom observation; and (6) participate in a focus group at the end of the intervention. Each PE teacher will recruit at least four classroom groups of no fewer than 16 students each, ensuring that at least 80% of the students in each group participate. Eligible students will be those aged 12–18 years from secondary schools. Participation will be completely voluntary and anonymous. School principals and students’ families will also be informed about the study’s aims and characteristics to obtain their informed consent for participation. The 80% participation rate applies only to baseline (T1); teachers not reaching it may be excluded, with replacements drawn from a waiting list. Dropout over time will not lead to exclusion if at least 60% of students complete all data points. The research team will make every effort to retain the full sample and minimize attrition throughout the study. Finally, the inclusion criteria for students’ participation in the intervention program will be: (1) obtaining consent from both parents/legal guardians and students; (2) commitment to completing the questionnaires assessing the study variables three times; and (3) regular participation in PE lessons.

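### Teachers are randomised, but the student tests of Hypotheses 1 and 2 treat students as independent, so their type I error exceeds the nominal 5%

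*Protocol article*

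**What the plan says.** The section on sample recruitment makes the teacher the unit of allocation: "Between 8–10 secondary PE teachers, assigned to the experimental group and to the control group equally". It also keeps teachers and schools one-to-one: "To minimize the risk of cross-contamination between conditions, teachers from the same high school will not participate". If several teachers from one school apply, a waiting list is used. On cluster size it says "Each PE teacher will recruit at least four classroom groups of no fewer than 16 students each". A participation floor of 80% per class applies at baseline. For later waves the rule is: "Dropout over time will not lead to exclusion if at least 60% of students complete all data points".

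The Plan of analysis then fixes the student analysis: "A 3 × 2 (Time × Condition) repeated measures MANCOVA will be performed for both teachers and students". The student covariates are age, sex, sociocultural background and school grade. A Time × Condition × Sex version follows, then Bonferroni-corrected paired t-tests within each arm. If parametric assumptions fail, Wilcoxon and Mann–Whitney tests replace them. Before any of this, "the assumptions of independence, linearity, and homogeneity of variance will be verified". No random effect, cluster-robust standard error or teacher-level summary is named.

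Nesting is suggested in one place only, the caption of Figure 2: "Hypothetical multilevel model of the predictive relationship between the study variables". That figure illustrates the mediation hypothesis (Hypothesis 3). The Plan of analysis describes the corresponding Mplus model as a longitudinal structural equation model and does not mention nesting.

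**The concern.** When whole teachers are allocated, the comparison between arms rests on 4–5 teachers per arm, however many students each brings. Students of one teacher share that teacher, the school and often the class. Any correlation among their answers adds variance to the arm difference that a student-level error term does not see.

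These outcomes give good reason to expect such correlation. Hypothesis 1 concerns students' ratings of the one teacher they share. The study aims describe class cohesion as a group-level factor. Academic performance is a PE grade received within one teacher's classes. The Limitations section expects the number and intensity of strategies used to vary between groups, which points to teacher-level variation in change as well as in starting level.

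Checking independence does not help. The allocation breaks it by design, and the named fallback tests also assume independent students. A significant result for Hypothesis 1 or 2 could therefore reflect chance differences between a handful of teachers. Because the article names the test, covariates, fallbacks and software, this is a stated method that does not fit the allocation, not a detail left to another document.

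**Working it through.** **The plan's own figure.** The only sample-size figure is 385 students. The single-proportion precision formula with p = 0.5 gives 1.96² × 0.25 / 0.05² = 384.16, rounded up to 385, before any non-response allowance. It contains no cluster term and no ICC, so it neither supports nor answers this point. Its other problems are a separate matter.

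**Inputs from the document.** Teachers: 8–10, equally split. Students per teacher: 4 × 16 = 64 at the minimum class size, or 64 × 0.80 = 51.2 at the participation floor, which is 12.8 per class.

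**Assumed, because the document gives none.** ICC of the analysed score. For Time × Condition this is the ICC of the change score. A two-sided 5% level is also assumed.

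**Formulas.** Design effect DE = 1 + (m − 1) × ICC. True SE / naive SE = √DE. Actual error = 2 × [1 − Φ(1.96/√DE)].

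**Clustering by teacher, m = 51.2**

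| ICC | DE | SE ratio | Effective N of 410 (8 teachers) | Actual error |
|---|---|---|---|---|
| 0.01 | 1.50 | 1.23 | 273 | 11.0% |
| 0.02 | 2.00 | 1.42 | 204 | 16.6% |
| 0.05 | 3.51 | 1.87 | 117 | 29.5% |
| 0.10 | 6.02 | 2.45 | 68 | 42.4% |

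Example at ICC 0.05: DE = 1 + 50.2 × 0.05 = 3.51, and 410/3.51 = 117.

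**Other cluster sizes.** With m = 64 the error is 12.5%, 19.2%, 33.6% and 46.8% at the same four ICCs. With 385 students over ten teachers (m = 38.5) it is 9.5%, 13.8%, 24.8% and 36.8%.

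**Clustering by class only, m = 12.8.** DE = 1 + 11.8 × ICC = 1.24, 1.59 and 2.18 at ICC 0.02, 0.05 and 0.10. The error is about 8%, 12% and 18%.

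**Simulation check.** Change scores were simulated with no effect and analysed with a student-level two-sample t-test. Ten teachers with four classes of 13 gave 16.6%, 30.2% and 43.2% at teacher ICC 0.02, 0.05 and 0.10. Splitting the correlation as 0.02 teacher plus 0.03 class gave 20.7% (23.7% with 16 per class). With ten per class, near the 60% retention floor, the error was about 10%, 26% and 38% at teacher ICC 0.01, 0.05 and 0.10. A t-test on teacher means stayed between 4.7% and 5.4% in every setting.

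**Paired t-tests.** Taking Bonferroni over three time pairs (0.05/3 = 0.017), with four classes of 16, the per-test error was about 6%, 24% and 38% at teacher ICC 0.01, 0.05 and 0.10, against a nominal 1.7%.

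**Precision.** Smallest effect detectable with 80% power at teacher level, m = 64, ICC 0.05: 0.61 SD with 8 teachers and 0.52 SD with 10. If students were independent: 0.25 and 0.22 SD.

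**The case against.** The best reply is that the size of the inflation is unknown. The document gives no ICC. The relevant one is that of the change score, which may be lower than the cross-sectional value. Part of the correlation may lie at class rather than teacher level, and that inflates less. The check also uses one outcome and no covariates, not the planned multivariate test. All of this stands and is why a range is shown. None of it brings the error back to 5%. The class-only case is a lower bound, since ratings of a shared teacher will also cluster by teacher.

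A reader might infer more than the document supports:

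- **Hypothesis 3.** One might conclude that the mediation test is also shown to be anti-conservative. It is not. That test belongs to the Mplus model. The Figure 2 caption calls the model multilevel, the figure cannot be seen here, and the one-sentence description in the Plan of analysis omits nesting without ruling it out. This is an ambiguity to settle.
- **Confidence intervals and effect sizes.** The plan announces no confidence intervals for effects, so none can be called wrong. Calling partial eta squared uninterpretable would also go too far. The demonstrated fault is in standard errors and p-values.
- **The teacher MANCOVA.** It uses teachers as its units, so this point does not affect it.

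The article's description of the trial simply as an RCT is a matter of reporting. The allocation unit itself is openly stated.

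**Conclusion.** The point holds for the student tests of Hypotheses 1 and 2: both MANCOVAs, the paired t-tests and the Wilcoxon and Mann–Whitney fallbacks. As written they do not hold a 5% level, and this must be corrected before analysis. The direction is certain given any positive intraclass correlation. The size rests on assumptions: roughly 17%, 30% or 43% at a teacher-level change-score ICC of 0.02, 0.05 or 0.10 with about 51 students per teacher; about 10–12% at 0.01; and about 8%, 12% or 18% at 0.02, 0.05 or 0.10 if clustering is by class only. Hypothesis 3 is not included in this conclusion.

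**What to change.** 1. For each student outcome, replace the MANCOVAs, paired t-tests and rank-test fallbacks with one of two analyses. The first is a mixed model with random effects for teacher, class and student and small-sample degrees of freedom based on the number of teachers. The second is a comparison of T1-adjusted teacher means on about 6–8 degrees of freedom (8 − 2 to 10 − 2).
2. With teacher means, add a permutation check over the possible equal allocations: 70 for 8 teachers, 252 for 10. The smallest attainable two-sided p-value is 2/70 = 0.029 or 2/252 = 0.008, so either size can reach 5%.
3. Describe the trial as cluster-randomised, and state the sample size in teachers with an assumed ICC.
4. Reconcile the Figure 2 caption with the description of the Mplus model, saying how nesting is handled. Treat the Hypothesis 3 mediation as exploratory, because 8–10 teachers cannot support a full between-teacher model.

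**Cost.** No new data are needed. Reported precision will be lower (about 0.5–0.6 SD detectable at ICC 0.05, against 0.22–0.25 SD under independence), and fewer results will reach significance. With teachers capped at ten, the plan should say openly that only large effects can be established.

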#### Aim 2: effects of teacher program on teachers

As for the second objective, most SDT-based training programs in PE have primarily examined their effects on students (Vasconcellos et al., 2020). However, preliminary evidence also suggests that these training programs can be beneficial for teachers as well (Reeve and Cheon, 2021). Thus, using a mixed-method approach, the second aim will be to examine the effects of the training program on teachers’ beliefs, feasibility, and intention to apply relatedness-supportive and class cohesion strategies, use of relatedness-supportive behaviors, and relationship satisfaction with students. In line with this aim, it is hypothesized that, by T2, experimental group teachers will perceive improvement in beliefs, feasibility, and intention to apply relatedness-supportive and class cohesion strategies, use of relatedness-supportive behaviors, and relationship satisfaction with their students, compared to those who do not receive any training (Hypothesis 4). Due to the scarcity of prior research, we will not posit specific hypotheses about the intervention’s long-term (T3) effects on the study variables. If enough male and female teachers participate in the training program, the intervention’s effects on the study variables will also be examined by sex.

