#### Teacher training program

Experimental PE teachers will participate in a training program designed to help them provide relatedness-supportive and class cohesion strategies while avoiding relatedness-thwarting behaviors. The training will be delivered by three experienced researchers in designing and implementing motivational teacher development programs, ensuring a close trainer-to-teacher ratio (~3 trainers per 4–5 teachers) to support implementation quality and fidelity.

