##### Teacher interpersonal behavior

To assess teachers’ need-supportive and need-thwarting behaviors, the PE Spanish version of the Interpersonal Behaviors Questionnaire (Burgueño and Medina-Casaubón, 2021) will be adapted to teachers. The scale begins with the stem “In PE classes … “followed by 24 items (four items per factor) that measure autonomy (e.g., “… I encourage them to make their own decisions”), competence (e.g., “… I acknowledge their abilities to achieve their goals”), and relatedness support (e.g., “… I show interest in their activities”), as well as autonomy (e.g., “… I restrict their ability to make decisions”), competence (e.g., “… I question their ability to make progress”), and relatedness thwarting (e.g., “… I do not show interest in them”). It is important to note that although this study primarily focuses on supporting relatedness-supportive behaviors and avoiding relatedness-thwarting behaviors, we will also include autonomy- and competence-supportive/thwarting behaviors to control for their potential effects. Responses will be assessed using a 5-point Likert scale, ranging from 1 (*strongly disagree*) to 5 (*strongly agree*).

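### The teacher-level repeated-measures MANCOVA cannot be estimated as specified on 8–10 teachers; Hypothesis 4 needs a simpler prespecified comparison

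*Protocol article*

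**What the plan says.** On numbers, Sample recruitment with inclusion criteria plans "Between 8–10 secondary PE teachers, assigned to the experimental group and to the control group equally", and adds that "the maximum number of participating teachers will be set at ten". The Teacher training program section, with "3 trainers per 4–5 teachers", confirms that 8–10 is the total and that each arm has four or five.

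On analysis, the Plan of analysis states: "A 3 × 2 (Time × Condition) repeated measures MANCOVA will be performed for both teachers and students". The teacher covariates, introduced as examples, are age, sex, "teaching experience, type of school, and school location for teachers". It continues: "a 3 × 2 × 2 (Time x Condition x Sex) repeated measures MANCOVA will be performed for both teachers and students". Mann–Whitney (between groups) and Wilcoxon signed-rank (within groups) tests are named for the case where parametric assumptions fail. Bonferroni-corrected paired t-tests follow within each group. Partial eta squared is labelled large above 0.14.

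On the hypothesis, Aim 2 compares trained with untrained teachers by T2 on five outcomes: beliefs, feasibility, intention, relatedness-supportive behaviors and relationship satisfaction. Aim 2 makes the teacher sex analysis conditional: "If enough male and female teachers participate in the training program". The Discussion's list of ten contributions likewise limits it to where it is feasible.

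**The concern.** One model is prescribed for two very different samples: several hundred students and at most ten teachers. A multivariate test needs at least as many error df as it has contrasts, because otherwise its error matrix cannot be inverted. Five outcomes at three times, with five covariates, looks far beyond what ten teachers can carry.

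If so, the main quantitative analysis of Aim 2 will return no multivariate test when it is run. The document does not say what would then be dropped (covariates, outcomes or the multivariate step), so that choice could be made with the data in view. Falling back on univariate output with 1–3 error df also invites over-reading of effect sizes.

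**Working it through.** The plan gives no sample size, power or df figure for teachers, so there is none to reproduce. The number of teachers is set by resources.

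**Inputs.** N = 8 to 10 teachers (Sample recruitment with inclusion criteria). Outcomes p = 5 (Aim 2). Three times, so 2 within-teacher contrasts per outcome. Listed covariates k = 5 (Plan of analysis). Assumed: one questionnaire per teacher per wave, binary school type and location, all five outcomes in one model, and no missing data.

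**Error df.** N − 1 (intercept) − 1 (condition) − k.
- k = 5: 8 − 7 = 1; 9 − 7 = 2; 10 − 7 = 3.
- k = 0: 8 − 2 = 6; 9 − 2 = 7; 10 − 2 = 8.

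**Requirements.** The between-teacher multivariate test needs error df ≥ p = 5. The doubly multivariate Time × Condition test needs error df ≥ 2p = 10. The averaged (sphericity-based) multivariate test needs 2 × error df ≥ p = 5. Matrix ranks were confirmed on simulated designs:

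| N | Covariates | Error df | Rank of 10 × 10 Time × Condition error matrix | Rank of 5 × 5 averaged error matrix |
|---|---|---|---|---|
| 8 | 5 | 1 | 1 | 2 |
| 9 | 5 | 2 | 2 | 4 |
| 10 | 5 | 3 | 3 | 5 |
| 8 | 0 | 6 | 6 | 5 |
| 9 | 0 | 7 | 7 | 5 |
| 10 | 0 | 8 | 8 | 5 |

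The doubly multivariate Time × Condition test is singular in every row. It would need 2 + 5 + 10 = 17 teachers with five covariates, or 2 + 10 = 12 with none; the cap is 10. With five covariates the between-teacher multivariate test is also singular (1–3 against 5), and the averaged test exists only at N = 10.

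**Univariate tests with five covariates.** These exist, with two-sided 5% critical t = 12.7 on 1 df (N = 8) and 3.18 on 3 df (N = 10). With no true effect, and under normality and sphericity, partial eta squared for Time × Condition follows a Beta(1, error df) distribution. Its mean is 1/(1 + error df), and P(> 0.14) = 0.86^(error df).
- Five covariates: mean 0.50 (N = 8) and 0.25 (N = 10); P = 0.86 and 0.86³ = 0.64.
- No covariates: P = 0.86⁶ = 0.40 (N = 8) and 0.86⁸ = 0.30 (N = 10).

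**Fallback tests, smallest attainable two-sided p.**
- Mann–Whitney, 2/C(2n, n): 2/70 = 0.029 (4 v 4); 2/252 = 0.0079 (5 v 5).
- Wilcoxon within one arm, 2/2ⁿ: 2/16 = 0.125 (n = 4); 2/32 = 0.0625 (n = 5). It can never reach 0.05.

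**Sensitivity of a simple comparison.** An unadjusted two-sided t-test at 5% has 80% power only for a standardized difference of 2.38 (4 v 4, 6 df) or 2.02 (5 v 5, 8 df). The protocol does not plan this test; the figures only show the scale.

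**The case against.** The strongest reply is that Hypothesis 4 is not left without an analysis, and that is right. A reader might infer from the singular matrices that no workable test exists. The Plan of analysis names Mann–Whitney, which can be computed at these sizes and can fall below 0.05. Aim 2 is also mixed-method, and the focus group covers perceived change in the teacher variables. Two limits remain. Mann–Whitney is triggered by failed parametric assumptions, not by a shortage of df. The focus group includes only experimental teachers, so it cannot supply the contrast with controls; nor can the within-group paired t-tests.

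Second, the covariate list is illustrative, and the plan does not say that all five outcomes enter one model. With few or no covariates, averaged and univariate tests exist, so the 1–3 df apply only to the full list. But the doubly multivariate Time × Condition test of five outcomes fails with no covariates at all, so trimming the list does not rescue it.

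Third, the Teachers' measures section asks teachers to answer with their selected student groups in mind. That could mean one questionnaire per class, or 32–40 rows at four classes each. Software would then return a test, but the rows would be clustered within the same 8–10 randomized teachers.

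Two further inferences should not be drawn. One is that error df would be negative because "we will also include autonomy- and competence-supportive/thwarting behaviors to control for their potential effects": the Plan of analysis does not list those scales as covariates, and nothing says that all would be added to the other five. The other is that the sex model certainly has 0–2 df: that assumes the other four covariates carry over, which is not stated, and the analysis is conditional elsewhere in the article. What stands there is an inconsistency between sections.

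**Conclusion.** The point holds as a mismatch between a stated analysis and a stated sample. The teacher 3 × 2 MANCOVA as specified leaves 1–3 error df, and its multivariate Time × Condition test of the five outcomes needs at least 10; removing every covariate gives only 6–8. This rests on one row per teacher per wave, 1-df covariates, and joint analysis of the five outcomes. It is not a detail that a fuller analysis plan could simply fill in, because the article fixes both the model and the cap of ten.

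It does not follow that Hypothesis 4 is untestable. It rests on a low-powered fallback whose trigger does not fit the problem. The student hypotheses are untouched. Separately, the teacher sex analysis is unconditional in the Plan of analysis and conditional in Aim 2 and the Discussion; these should be reconciled.

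**What to change.** In the Plan of analysis, for teachers only:

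1. Replace the MANCOVA and its covariates with a prespecified between-arm difference in T1-to-T2 change for each Hypothesis 4 outcome. Give a 95% CI (6 df at 4 v 4, 8 df at 5 v 5) and an exact permutation or Mann–Whitney p-value, not dependent on assumption checks.
2. Show each teacher's T1, T2 and T3 scores.
3. Do not apply the small, moderate and large partial eta squared labels to teacher results.
4. Label Hypothesis 4 exploratory. Read it with the focus group, noting that this covers experimental teachers only.
5. Make the teacher sex analysis conditional and descriptive, to match Aim 2 and the Discussion.

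The cost is the loss of covariate adjustment for teachers and a weaker claim for Hypothesis 4. No extra data or teachers are needed. Balancing school type and location at allocation is a separate, optional step; it would change the randomization, so it is more than an edit to the analysis text.

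### With 4–5 teachers per arm, the exact two-sided within-arm Wilcoxon fallback for teacher outcomes cannot reach p < 0.05; smaller approximate p-values would not be reliable

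*Protocol article*

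**What the plan says.** Under Sample recruitment with inclusion criteria, the protocol plans for "Between 8–10 secondary PE teachers, assigned to the experimental group and to the control group equally", and adds that "the maximum number of participating teachers will be set at ten". That gives 4 or 5 teachers per arm.

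Under Plan of analysis, a Time × Condition repeated-measures MANCOVA is planned for teachers and for students. Should the parametric assumptions fail, the same paragraph provides a fallback for change within an arm: "appropriate non-parametric alternatives such as the Wilcoxon signed-rank test (for within-group comparisons"). For contrasts between the arms, the fallback is a different one: "the Mann–Whitney U test (for between-group comparisons) will be used". Bonferroni-corrected paired t-tests of change within each group are also planned. One threshold covers everything: "For all analyses, the significance threshold will be set at *p* < 0.05". The paragraph does not say whether p-values are exact or asymptotic, or whether they are one- or two-sided.

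Under Aim 2, the teacher hypothesis is that trained teachers improve by T2 "compared to those who do not receive any training (Hypothesis 4").

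**The concern.** The protocol fixes the test, the threshold and the number of teachers, and for teachers the three do not fit together. A signed-rank test on 4 or 5 pairs has so few possible sign patterns that the most favourable result may still miss the threshold. A non-significant result would then say nothing about whether teachers changed, yet it could be reported as no improvement. If the software prints an asymptotic p-value instead, the same data could be reported as significant although the exact p-value is above 0.05.

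The fallback is a realistic route for teachers. Normality and homogeneity of variance can hardly be verified with 4 or 5 people per arm on short 5-point scales and one single 10-point item.

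**Working it through.** **Inputs.** Teachers per arm: n = 4 or 5 (8–10 in total, equal split, maximum ten). Threshold: 0.05. Assumptions: one score per teacher per time point; two-sided testing, with one-sided shown as the range. The protocol gives no power, minimum p or sample size for the teacher analysis, so there is no stated figure to reproduce.

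**Exact signed-rank test.** Under the null hypothesis each of the 2^n sign patterns is equally likely. The most extreme result is that all changes go in one direction.
- Two-sided minimum p = 2/2^n: n = 4, 2/16 = 0.125; n = 5, 2/32 = 0.0625.
- One-sided minimum p = 1/2^n: n = 4, 1/16 = 0.0625; n = 5, 1/32 = 0.031.
- The first size that passes two-sided is n = 6, with 2/64 = 0.031. That needs 12 teachers under equal allocation, and the cap is ten.
- A teacher with no change drops out of the ranking. Five teachers with one zero change are therefore in the n = 4 case.

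**Normal approximation, no continuity correction, all changes in one direction.** Z = (sum of ranks / 2) / √(sum of squared ranks / 4).
- n = 5, untied: Z = 7.5/√(55/4) = 7.5/√13.75 = 2.02, p = 0.043. With ties, p lies between 0.025 and 0.042.
- n = 4, untied: Z = 5/√(30/4) = 5/√7.5 = 1.83, p = 0.068. Only four equal changes go below 0.05: Z = 5/√(25/4) = 2.00, p = 0.0455.
- With a continuity correction the untied values are 0.059 (n = 5) and 0.100 (n = 4).

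The approximate test is too liberal at n = 5. With untied changes it rejects only when all five agree: if the smallest change is reversed, Z = 6.5/√13.75 = 1.75 and p = 0.080. The null probability that all five agree is 2/32 = 0.0625, so the nominal 5% test rejects 6.25% of the time.

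**If the Bonferroni correction also applied.** It is stated for the paired t-tests, not for Wilcoxon. For three time contrasts the level would be 0.05/3 = 0.0167. No two-sided version reaches that (smallest 0.025), and neither does the exact one-sided test (0.031).

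**Exact Mann–Whitney test between arms.** Two-sided minimum p = 2/C(2n, n): 4 v 4, 2/70 = 0.029; 5 v 5, 2/252 = 0.008. Both are below 0.05.

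**The case against.** A reader might infer that teacher improvement can never be shown, or that the plan forces a finding of no improvement on every teacher outcome. The documents do not support that.

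- The Wilcoxon test applies only if parametric assumptions fail, and it is introduced as an example.
- Hypothesis 4 compares trained with untrained teachers. The sentence that names Wilcoxon also names a between-group test, and that test can reject at this size.
- The MANCOVA and the paired t-tests remain, and Aim 2 also draws on a focus group of the trained teachers.
- Students are covered by the same sentence, but with a planned minimum of 385 the floor on p is irrelevant to them.

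All of this stands, and it confines the point to one conditional comparison.

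It can also be said that neither exactness nor sidedness is stated, and that such details are often left to an analysis plan. That is fair, and it means that a p-value below 0.05 is not impossible under every reading. It does not rescue the test. The asymptotic p-value is not valid at this size, and a one-sided exact test could pass with 5 teachers but not with 4.

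Finally, the Measures section asks teachers to answer with their selected student groups in mind. If this produced one score per class, there would be more pairs, but they would not be independent, which is a different difficulty.

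The protocol does not say whether the Mann–Whitney test is applied to T2 scores or to change. Applying it to change is one permitted reading, so that part of the remedy is partly a clarification.

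**Conclusion.** The point holds in a limited form. For teacher outcomes, with 4–5 teachers per arm and one score per teacher per time point, the exact two-sided within-arm Wilcoxon test cannot give p below 0.125 or 0.0625. An approximate two-sided p below 0.05 would reflect the approximation and not the strength of the evidence. On neither reading does the named test give a usable two-sided result at the stated threshold. The between-arm test of Hypothesis 4, the parametric analyses and the student analyses are unaffected. It is a modest fault in a fallback, but it arises from figures the protocol itself fixes, and it is cheap to remove.

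**What to change.** For teacher outcomes, drop the within-group Wilcoxon test as a significance test. Show each teacher's T1, T2 and T3 values and describe the within-arm changes. Name, as the non-parametric test of Hypothesis 4, an exact Mann–Whitney or permutation test of the T1-to-T2 change between trained and control teachers, and state that exact two-sided p-values are used. The student fallback need not change on this account.

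The cost is one or two sentences, with no extra teachers or data. Within-arm teacher changes would carry no p-value, and the fallback test would not be covariate-adjusted.

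The replacement is able to reject but is not powerful. The protocol gives no teacher effect size. On assumed normal change scores, simulated power at 4 v 4 and 5 v 5 is about 14% and 21% for a between-arm difference of 1 SD of change, 48% and 68% for 2 SD, and 82% and 95% for 3 SD. A non-significant teacher result should therefore still be read with caution.
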